## Abstract

**Background:**

Retention in care and adherence to antiretroviral therapy (ART) among people living with human immunodeficiency virus (PLHIV) is a critical challenge in many African countries including Burkina Faso. Delivering text messaging (short message service, SMS) interventions through mobile phones may help facilitate health service delivery and improve patient health. Despite this potential, no evaluations have been delivered for national scale settings to demonstrate the impact of mobile health (mHealth) for PLHIV.

**Objectives:**

This study aims to test the impact of SMS text messaging reminders for PLHIV in Burkina Faso, who are under ART. The evaluation identifies whether patients who receive SMS text messages are more likely to (1) retain in care (measured as a dichotomous variable), (2) adhere to antiretroviral regimens (measured as the number of doses missed in the past 7 days), and (3) experience slower disease progression (measured with T-lymphocytes cells). The second objective is to assess its effects on the frequency of health center visits, physical and psychosocial health, nutrition and whether the type of message (text vs image) and frequency (weekly vs semiweekly) have differential impacts including the possibility of message fatigue over time.

**Methods:**

This 24-month, wide-scale intervention implements a randomized controlled trial (RCT) to evaluate the impact of four variants of a mHealth intervention versus a control group. Our sample comprises adult patients (>15 years of age) undergoing antiretroviral therapy with access to mobile phone services. Multivariate regression analysis will be used to analyze the effect of the intervention on the study population. Data collection is done at baseline and three follow-up waves 6, 12, and 24 months after the intervention starts.

**Results:**

The targeted 3800 patients were recruited between February 2015 and May 2015. But political uncertainty delayed the launch of the intervention until October 2015. Data analysis has not yet started. The first follow-up data collection started in April 2016. To the best of our knowledge, this is the first research that explores the effects of mobile message reminders using a wide-spread sample across an entire nation over a 2-year horizon, especially in a Francophone African country.

**Conclusions:**

We hypothesize that the interventions have a positive impact on retention in care and adherence to ART schemes and that a more sluggish disease progression will be observed in the short run. However, these benefits may fade out in the long run. The study expects to advance the research on how long mHealth interventions remain effective and when fatigue sets in the context of wide-scale interventions. This information will be useful in designing future wide-scale mHealth interventions in developing countries.

## Introduction

### Background

Several factors inhibit retention in care and adherence to antiretroviral therapy (ART) among people living with human immunodeficiency virus (PLHIV). Typical reasons include individual and social obstacles, such as lack of information on treatment procedures, social stigma, discrimination, and competing priorities that prevent patients from considering antiretroviral treatment as a worthwhile investment of time, energy, or resources [1,2]. In developing countries, economic and contextual barriers may further amplify these challenges because patients are resource-constrained and health facilities may not be easily accessible leading to substantial costs in terms of wage losses and travel expenses [3].

Discontinuation of ART regimens is particularly prevalent in Sub-Saharan Africa. Systematic reviews have found that approximately 22.5% of patients discontinue ART within 10 months and 56% are lost to follow-up or death during the first 2 years of the treatment [4,5]. HIV patients are perhaps not fully aware of the long-term consequences of dropping out from ART treatment. Lack of retention in care and adherence to antiretroviral therapy increases HIV viral loads and the probability of transmission, reduces the number of T-lymphocytes cells in the blood (CD4 count)-an indicator of how well the immune system is working and a strong predictor of HIV progression-leads to deterioration in the quality of life and can be responsible for creating virus strains that are resistant to current HIV medication [6-9]. Favorable health outcomes for PLHIV require lifelong compliance with ART programs. At the macro-level the negative side effects of poor compliance with ART can deteriorate the efficiency and efficacy of public health care systems by increasing the burden of the disease and the potential costs of care in the future [10-12].

The World Health Organization (WHO) promotes the use of innovative mobile technologies to overcome barriers that undermine access to health care and the quality of care delivery in resource-poor countries [13]. mHealth is an important element of this approach as it can help alleviate some of the existing obstacles in the delivery of quality care [14-16]. Mobile technologies may help patients undergoing ART to maintain the treatment routine as they provide instant communication unrestricted to location [17,18]. Specifically, the use of text messaging (short message service, SMS) reminders may support PLHIV to take their pills every day, schedule refills of their prescriptions, and assist them through common side-effects. Such reminders are considered to be a low-cost, low-barrier intervention [19]. Especially in resource-constrained developing countries where some patients live far from the health centers and a system of regular home visits by health care providers is not in place [1-3], regular text messages may help patients to remain in care and adhere to their antiretroviral regimens [20-22]. These advantages have promoted the rapid expansion of mHealth projects that aim to improve health outcomes in patients living with HIV and other diseases across the developing world [23].

Despite the possibility of cost-efficient, easy outreach through SMS, recent studies have shown contrasting evidence. While several studies have demonstrated that mobile text message reminders are effective in enhancing adherence to ART programs [24-28] others do not find any effects [29,30]. Research in Kenya demonstrates that 53% of the participants who received weekly SMS reminders achieved adherence of at least 90% during the 12 months of the study [24]. In the control group, only 40% of the participants achieved similar adherence levels. Evidence from a small study in Brazil also suggests that adherence to ART increased due to text message reminders at least during the 4-month study period [28]. In contrast, a 6-month study in Yaoundé, Cameroon, found that standardized motivational mobile text messages did not increase adherence [29]. Likewise, research conducted in some states in India did not find a statistically significant impact of mobile phone reminders on time to virological failure or ART adherence at the end of a 2-year study period [30]. Moreover, we are not aware of any long-term study that has been conducted in a Francophone African country where perceptions, preferences, and health systems are considerably different as compared with Anglophone African countries [31].

### Justification

The background provided above motivates continued research on the impact of mHealth interventions in developing countries. The majority of the existing studies are limited to geographically circumscribed areas such as capital centers, and are based on small sample sizes or on short-time horizons [24-30]. For instance, the Brazilian study carried out a 4-month study with as few as 21 Brazilian female PLHIV [28]. Similarly, the 2 studies in Kenya followed less than 550 participants and included no more than 3 health facilities for a period of 12 months [24,27]. The intervention in Cameroon included 1 hospital and 198 participants for a period of 6 months [29]. While the intervention in India had the longest time horizon of 2 years and a relatively large sample of 631 participants it was based on data from 3 health centers located in only 2 states [30]. Thus, research based on a sample across an entire nation with a longer-term horizon is warranted. The present study is timely as it is based on a wide-spread intervention across Burkina Faso with a 2-year horizon. These design features improve the study’s external validity. Furthermore, the study will enhance our understanding of the extent to which mHealth interventions promote healthy behaviors and support psychosocial wellbeing. Therefore, the study will contribute to an improved understanding of when, why, and for whom mHealth interventions work [32,33].

### Objectives

The main objective of this trial is to determine the impact of four different packages of SMS message reminders to promote HIV patients’ retention and adherence to ART as well as their health outcomes in a large-scale randomized controlled trial (RCT) in a Francophone country, namely Burkina Faso. We hypothesize that patients who receive text messages are encouraged to take their pills and reminded of the importance of ART for their health so that they remain in care longer than those who do not receive text messages. We also anticipate that enhanced retention and adherence will lead to positive health outcomes. Our objectives are (1) to inform best practices for enrolling PLHIV into ART programs and supporting them throughout care, (2) to provide insights on the key obstacles confronting patient retention and adherence to ART, (3) to advise on the most effective application of mobile technology for health interventions, including the short-, medium-, and long-term benefits that can be anticipated, and (4) to encourage long-term patient success with ART by promoting feasible and efficient strategies that may be adopted in resource-constrained settings. Concerning the effectiveness of SMS text messaging reminders, our intervention includes two complementary objectives. First, the study evaluates whether patients may experience fatigue from the SMS text messaging reminders. By carrying out 3 surveys at 6, 12, and 24 months after the launch of the intervention, we aim at determining the optimal period for such a type of mHealth intervention to be efficient. Second, the trial will evaluate the effects of message type (text vs ASCII image) and frequency (weekly versus semi- *weekly)*
*,* i.e., the differences in the four treatment arms, on patient outcomes.

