### Study Design

The study design rests on a five-arm, randomized, controlled trial with four treatment arms and one control group. With the support of the Burkinabe Ministry of Health and local health centers, HIV patients have been screened and recruited at 80 health care facilities that provide antiretroviral therapy across the 13 regions of Burkina Faso. Using a 7:7:7:7:10 allocation ratio, patients are randomized to one of the five-arms with the control group being slightly oversampled as we introduce two types of control groups; a control group of patients drawn from health centers which do not receive any of the interventions and a spillover-prone control group drawn from health centers which are visited by both treated and untreated patients. A member of the international survey team carried out the randomization in Stata. The team member did not have any interactions with patients. Once patients were randomly allocated, the intervention was launched and the SMS messages are sent. Patients in each of the five groups receive the public standard care but only four groups receive an SMS reminder that varies by the type of message (text versus American standard code for information interchange (ASCII) image) and its frequency (weekly vs semiweekly). The study collaborates with the health care personnel attending to the patients as well as the associations and self-help groups that provide psychosocial support to PLHIV. The former provide medical information and the latter carry out the survey interviews. The health personnel and the enumerators are not informed about the outcome of the random allocation of the participants. Because they do not know which patient is in which group, we do not expect bias. The study will keep track of the patients 6, 12, and 24 months after the intervention is launched.

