
### Intervention

The intervention comprises 4 treatment groups and 1 control group to investigate the impact of different types of SMS text message reminders sent out at different frequencies on patient outcomes. For groups 1 to 4, messages will be sent on a weekly basis. Patients of each of the 4 treatment groups will receive at least 1 text or image message per week. Image messages are used to ensure that the intervention reaches out to people with limited literacy skills and they will be sent as ASCII pictures. Because we do not expect the participants to have smartphones, we use ASCII images that can be displayed on basic mobile phones. The content and frequency of the messages will vary for each of the 4 treatment groups. While the first treatment group will receive only 1 text message per week (low frequency), the second treatment group receives a total of 2 text messages per week (high frequency). Meanwhile, the third group will get 1 text and 1 image message per week and, the fourth group will receive 2 image messages per week. All messages will be sent at 8 am and patients will not be prompted to respond. The impact of the treatments will be assessed in follow-up surveys at 6, 12, and 24 months after the start of the intervention. A detailed identification of the 5 groups, type of interventions, and timings are presented in Table 1.

**Table 1 table1:** Identification of the five intervention groups.

Treatment arms		Intervention (per week)	Timing

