### Duration and Follow-Up Surveys

The intervention will run for a period of 2 years. We will conduct four outcome assessments during baseline as well as 6, 12, and 24 months into the intervention.

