#### Secondary Outcomes

Information on 5 groups of secondary outcomes will be collected. First, we will obtain information about the incidence and number of missed health center visits. Second, because we are also interested in more general physical and psychosocial health aspects we will gather information about the body mass index, the incidence of coinfections, mortality, as well as subjective and mental health ratings. In addition, we will collect information on the patients’ levels of risk preference and their subjective discount factors. Third, we will also measure nutritional outcomes. Fourth, to assess design effects and the duration of effectiveness of the mHealth intervention, we will gather data on the message type and frequency. The sensitivity to message type (text vs ASCII image) and the frequency (weekly vs semiweekly) of receiving the messages will be measured by comparing the effects of the 4 different interventions on the primary outcomes [24-30]. Finally, message fatigue will be measured using patients’ perceptions and possible changes in the impact on the primary outcome indicators across follow-up survey rounds. The secondary outcomes will be measured 6, 12, and 24 months after commencement of the intervention.

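### The aim of finding the optimal period for the messages goes further than the design: all messaged arms run the same 2 years, so the trial can show waning under continued messaging but not an optimal duration

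*Protocol article*

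**What the plan says.** All references are to the Protocol article.

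- **Aim.** Objectives introduces message fatigue as the first of two complementary objectives. It then says of the three follow-up surveys that "we aim at determining the optimal period for such a type of mHealth intervention to be efficient".
- **Length of messaging.** Duration and Follow-Up Surveys gives one length for the whole trial: "The intervention will run for a period of 2 years".
- **Assessments.** The same section states: "We will conduct four outcome assessments during baseline as well as 6, 12, and 24 months into the intervention". Study Design agrees: "The study will keep track of the patients 6, 12, and 24 months after the intervention is launched". Table 2 has no later column.
- **What differs between arms.** Intervention says: "The content and frequency of the messages will vary for each of the 4 treatment groups". It adds: "Patients of each of the 4 treatment groups will receive at least 1 text or image message per week". Neither that section nor Table 1 gives any arm an early stop, a late start or a change of allocation.
- **Planned analysis over time.** Secondary Outcomes measures fatigue by patients' perceptions and by "possible changes in the impact on the primary outcome indicators across follow-up survey rounds". The Analysis Plan adds a difference-in-difference model that uses the three follow-ups jointly.
- **Narrower wording elsewhere.** The abstract's Conclusions speak of "how long mHealth interventions remain effective and when fatigue sets in the context of wide-scale interventions", and the Conclusions of the Discussion are similar.

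**The concern.** To call one period of messaging optimal is to say that it does better than a shorter or longer one. That needs outcomes, at a common later time, for patients whose messages ran for different lengths. The trial has two assigned lengths: 24 months in the four messaged arms and none in the control group.

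The practical risk follows from the protocol's own hypothesis, which is that benefits may fade over time. Suppose the effect at 24 months is smaller than at 6 months. A programme could take a reported optimal period of 6 or 12 months as advice on when to stop reminders, although no patient in the trial was observed after messages had stopped. The protocol also means its results to inform the design of later large programmes, so the wording of this aim carries weight beyond the trial.

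**Working it through.** The plan gives no figure to reproduce here. The check is which effects the design identifies.

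**Notation.** Let E(d, t) be the difference from control at month t for patients messaged during the first d months. The candidate lengths are 6, 12 and 24 months, matching the surveys, and t is a survey month with t ≥ d.

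**What the design gives.** Every messaged patient is assigned d = 24. At month 6 such a patient has had 6 months of messages, so the month-6 survey yields E(6, 6). This assumes that messages still to come do not affect outcomes already measured. The same argument applies at months 12 and 24.

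| Messaging length | Month 6 | Month 12 | Month 24 |
|---|---|---|---|
| 6 months | E(6, 6): observed | E(6, 12): not observed | E(6, 24): not observed |
| 12 months | – | E(12, 12): observed | E(12, 24): not observed |
| 24 months | – | – | E(24, 24): observed |

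Three of the six cells are observed. These are the diagonal cells, where messages have run right up to the survey. The three unobserved cells are those where messages stopped before the survey. Nothing after month 24 is observed for any length.

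**What the diagonal answers.** Comparing E(6, 6), E(12, 12) and E(24, 24) shows whether the effect holds or wanes as messaging continues. Each is a randomised contrast with a concurrent control, so this comparison is sound, at three time points.

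**What an optimal period needs.** Whether a 6-month programme does as well as a 24-month one at month 24 depends on E(6, 24) − E(24, 24). The first term is never observed.

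**Illustration** (assumed effects, not from the documents). Suppose the trial finds E(6, 6) = 5 percentage points and E(24, 24) = 2 points.

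- If stopping at 6 months loses the whole effect, E(6, 24) = 0 and the contrast is 0 − 2 = −2 points: continuing is better.
- If stopping at 6 months preserves the effect, E(6, 24) = 5 and the contrast is 5 − 2 = +3 points: the shorter period is better.

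The trial's data would be the same in both cases, so they cannot decide between them. Neither a larger sample nor a different model would change this.

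**The case against.** The strongest reply is that the phrase is being read out of context. It completes the fatigue objective and may mean only the span over which messages keep working. The rest of the article fits that reading: the abstract, Secondary Outcomes and the Discussion all speak of fatigue or of how long the effect lasts. No section promises an estimate of the effect of stopping, and the Analysis Plan contains no estimator of an optimal period. The aim belongs to a complementary objective, and no primary analysis rests on it.

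Most of this stands, and it is why the point is minor. It does not remove the problem. Fatigue is already stated as an aim in the sentence before. The words optimal period add a prescriptive claim and tie it to a stated method, the three surveys, which cannot deliver it. If only the onset of fatigue is meant, the sentence should say so.

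Three stronger readings are tempting, and the documents do not support them.

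- *No comparison across time is possible.* This is too broad. The effects after 6, 12 and 24 months of continuous messaging are validly estimated and can be compared.
- *The statements on how long messages remain effective are wrong too.* They can be answered from those same three effects, provided they are understood as applying while messages continue.
- *A look at medical records after month 24 would supply the missing information.* All four arms stop together, so it would show only what persists after a 24-month programme and would not rank durations. Consent for records, under Eligibility and Informed Consent, also covers only the study period.

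**Conclusion.** The aim in Objectives is stated more strongly than the design supports. The trial can estimate the persistence or waning of the message-versus-control effect over up to 24 months of continuous messaging. It cannot identify an optimal duration or the effect of stopping at 6 or 12 months, because every messaged arm has the same length and no planned assessment follows the end of messaging.

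The point is minor. It limits one conclusion and touches no primary outcome, sample size, model or significance level.

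The conclusion assumes that messaging ends at 24 months and that the last survey falls at that time, as Duration and Follow-Up Surveys indicates. Should some 24-month interviews take place a little after messages end, they would still describe only patients messaged for the full 2 years.

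**What to change.** In Objectives, replace the optimal-period aim with wording such as: the three surveys will be used to estimate how far the effect of the messages persists or wanes over up to 24 months of continuous messaging; no conclusion will be drawn on the optimal duration or on the effect of stopping messages.

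The Conclusions of the abstract and of the Discussion need at most the qualifier *under continued messaging*. No change to data collection or analysis is needed, and no assessment after month 24 should be added for this purpose.

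The cost is one sentence and, at most, two short qualifiers. The only downside is a narrower claim. Results states that analysis of the intervention has not begun, so the claim can still be narrowed before any effect is seen. A statement that ranks durations would need a trial in which the length of messaging was itself randomised, with assessment after the shorter period had ended.

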## Methods

### Trial Setting

The study is implemented in the Francophone African country of Burkina Faso. The Joint United Nations Programme on HIV/AIDS (UNAIDS) reports that this country suffered a HIV prevalence of 0.9 in 2014 and the total number of PLHIV is estimated to be around 110,000 of which 94,000 are adults and 18,000 are children younger than 15 years [34]. The feminization of HIV is also observed in Burkina Faso since 59 percent of the adult PLHIV are women according to the National Council for the Fight against AIDS and Sexually Transmitted Infections (CNLS-IST) -the national committee in charge of the surveillance and fight against HIV/AIDS. The country provides free anti-retroviral treatment and its provision of HIV care follows WHO’s international guidelines and strategies [35,36]. Burkina Faso’s National Plan to combat HIV includes decentralization policies and multisector participation with the aim to increase the number of PLHIV who enroll at health centers that provide ART therapy and care [37]. Despite these efforts the fight against HIV and for ART adherence and retention remain a concern. Although the actual number of PLHIV enrolled in official files increased from 70,230 in 2013 to 76,342 in 2014, the actual number of patients undergoing active antiretroviral treatment was only 60% (42,145) in 2013 and 61% (46,623) in 2014. Similarly, despite the fact that the number of patients that becomes lost to follow up decreased almost by half from 2013 to 2014 (833 to 443), they are all attributed to fatalities [34]. These figures provide a first indication that adherence and retention to ART cannot be assured in Burkina Faso. And indeed, a survey carried out by UNAIDS in 2012 among 2,800 Burkinabe PLHIV revealed that adherence is perceived as a challenge due to negative side effects from treatment, the time and resources needed to regularly refill the stock of drugs and stigma [38]. The study we aim to implement allows us to assess whether and how retention and adherence may be improved.

